## Methods

### Design

We designed an 8-week, double-blind, randomized controlled trial, with two treatment arms: iFightDepression tool + TAU and internet-based psychoeducation + TAU. Participants will be randomly allocated (1:1) after the first assessment visit. Randomization will be performed electronically by an independent study researcher. Participants in both treatment arms will be followed via internet during a 12-week period.

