### Study participants

A total of 310 participants with major depressive disorder (MDD) diagnosis will be included in the study. Diagnosis will be made according DSM-IV-TR criteria and participants will be recruited from different mental health services (i.e., Red de Salud Mental de Guipúzkoa, Hospital del Mar, Hospital de la Santa Creu i Sant Pau, Hospital Parc Taulí and Hospital Universitario de la Princesa) and primary care facilities in their catchment areas. Sample size was established in order to detect an effect size of d = 0.2 with 95% power (SE = 0.5) and assuming a conservative correlation coefficient between pre-post measures of 0.5 and a drop-out of 20%. Sample size was calculated using G*Power 3.1.7 software.

Individuals meeting the following criteria will be eligible: 1) Participants of both genders 18 years old and older, 2) MDD diagnosis according to DSM-IV-TR criteria with mild-moderate symptoms according to the CGI-severity (scores ≤4), 3) minimum knowledge of internet use and availability of an internet device (tablet, computer, smartphone) and 3) given written informed consent. Exclusion criteria are: 1) suicidal ideation assessed by the HDRS and/or clinical interview, 2) psychotic symptoms related or not related to a mood disorder, 3) severe comorbidity axis I and axis II diagnosis, 4) currently receiving standard face-to-face CBT.

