### Study measures

Different types of variables will be collected (see Table 2) including socio-demographic characteristics of the sample (i.e., gender, age, ethnic group, marital status, living arrangements, educational level, employment status and annual income) and an exhaustive clinical history [i.e., age at MDD onset, number of previous MDD episodes, days in inpatient hospitalization (if applied), axis I and axis II diagnosis, and current pharmacological treatment].

**Table 2 Tab2:** Measures used by study period

Measure	Baseline assessments (Face to face)	Week 2 (Online)	Week 4 (Online)	Week 6 (Online)	Post-intervention assessment (Face to face)	12 weeks FU (online)
Demographic information (gender, age, marital status, etc.)	x					
Medical/Psychiatric History	x				x	
MINI (depression and suicide risk sections)	x				x	
Primary outcome measure:						
-HDRS	x				x	
Secondary outcome measure:						
-PHQ-9	x	x	x	x	x	x
-CGI-S					x	
-RDQ	x	x	x	x	x	x
-EuroQol-5D	x				x	
-FAST	x				x	
-Ad hoc satisfaction Questionnaire					x	

*Note*: *MINI* Mine-international Neuropsychiatric Interview, *HDRS* Hamilton Depression Rating Scale, *PHQ-9* Patient health Questionnaire, *CGI-S* Clinical Global Impression-Severity, *CGI-I* Clinical Global Impression-Improvement, *RDQ* Remission from Depression Questionnaire, *FAST* Functioning Assessment Short Test

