### Statistical analysis plan

SPSS v22.0 will be used for statistical analyses. Primary analyses will be conducted on the Intention-To-Treat (ITT) sample. Missing data will be inspected and handled via full information maximum likelihood (FIML) or multiple imputations (MI) as appropriate.

The primary outcome is change in HDRS scores from baseline to post-treatment (8 weeks). For primary and secondary outcome measures, repeated measures ANOVAs will be computed to examine pre-post treatment differences between groups.

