## Discussion

The present study aims at evaluating the efficacy of an internet-based self-management tool for moderate to mild depression compared with internet-based psychoeducation. Confirming the efficacy of the iFightDepression tool will entail important implications. As IFD could be easily prescribed it could potentially reach patients that usually remain untreated or have to wait for long-periods to receive psychological treatment. In addition, the availability of the both interventions in three different languages (Spanish, Catalan and Basque) aims at facilitating participant’s adherence. A strength of our study is that the recruitment will mainly take place in general practices, were patients with mild to moderate depression symptoms are often treated.

The risk of dropout constitutes one of the potential major obstacles of our study. We’ve tried to mitigate this by expanding our recruitment area to public health-care facilities located in three large areas of Spain (Catalonia, Madrid and Basque Country) and by providing specific language versions of the iFD tool and the psychoeducation web-page. As commented before, the design of our study privileges a naturalistic approach and therefore, participants will be recruited from primary care facilities in which most patients with mild/moderate symptoms of depression are visited and participants with concomitant ant depressive medication will be allowed in the study. Considering that the effects of the concomitant medication may impact our findings, a sub-analysis evaluating the potential effects of antidepressant will be conducted and participants will be excluded from the study if drastic changes in their medication took place during the study period.

In summary, the present study aims to provide evidence in regards to iFD tool as an add-on approach for individuals presenting mild to moderate symptoms of depression. Counting on a tool like iFD will facilitate its use in the public health care system, representing a treatment approach that can potentially reach a large amount of patients avoiding long waiting lists.

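### Baseline antidepressant use, which the plan says may affect the findings, is not named in the primary HDRS model; pre-specifying it would be a small, nearly free gain in precision

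*Protocol article*

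**What the plan says.** Four places in the protocol article bear on this.

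- **Discussion.** Concomitant antidepressants are allowed, and the article responds to their possible influence as follows: "Considering that the effects of the concomitant medication may impact our findings, a sub-analysis evaluating the potential effects of antidepressant will be conducted". The same sentence adds that participants with drastic medication changes during the study will be excluded.
- **Study measures.** The clinical history includes "current pharmacological treatment". Table 2 schedules the medical and psychiatric history at baseline and again at the post-intervention visit.
- **Statistical analysis plan.** The primary outcome is HDRS change from baseline to week 8, on the ITT sample. For the primary and secondary outcomes, "repeated measures ANOVAs will be computed to examine pre-post treatment differences between groups". No covariate is named.
- **Design.** "Participants will be randomly allocated (1:1) after the first assessment visit". No stratification factor is named here or under Procedure.

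**The concern.** The article singles out one pre-randomisation characteristic as able to affect its results, collects it, and then deals with it only outside the primary analysis. A sub-analysis by antidepressant use may be informative, but it does not change the primary estimate or its standard error.

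Treatment as usual includes drug treatment only if needed, so both arms will mix users and non-users. If users and non-users differ in how much their HDRS changes, two small costs follow. The variation they add stays in the error term. And if the arms happen to differ in their share of users, that difference stays in the estimate. With a target stated as d = 0.2, even small shifts are worth avoiding when this costs nothing. A pre-specified term also removes discretion: if a visible imbalance appeared in a variable already flagged as important, there would be pressure to adjust after seeing the data.

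**Working it through.** **Inputs from the article.** Total 310 ("A total of 310 participants with major depressive disorder (MDD) diagnosis will be included in the study"), 1:1 allocation, 20% drop-out, pre-post correlation 0.5, target d = 0.2, power 95%. Completers: 310 x 0.8 = 248, or 124 per arm.

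**Inputs assumed, not in the documents.** Share on an antidepressant at baseline, p = 0.3 to 0.7. Difference between users and non-users in HDRS *change*, g = 0.2 to 0.5 SD. Two-sided alpha 0.05.

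**1. The plan's own figure.** In a G*Power-type repeated measures ANOVA (two groups, two measurements, correlation 0.5), the between-factors test has noncentrality f² x N x 2/(1 + 0.5). With 0.2 entered as Cohen's f, 95% power needs N = 246, and 246/0.8 = 307.5, i.e. 308 against the stated 310. With 0.2 read as d (f = 0.1), the same test needs 978 and the group-by-time test 328 (1,223 and 410 after drop-out). The present point does not alter the sample size; this matters only for which target the shift below is compared with.

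**2. Units.** With correlation 0.5, the SD of change is sqrt(2 x (1 - 0.5)) = 1 single-visit SD, so SD units carry over to the change outcome.

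**3. Chance imbalance.** The 95% limit is 1.96 x sqrt(2p(1-p)/124).
- p = 0.3 or 0.7: 1.96 x 0.0582 = 0.114
- p = 0.5: 1.96 x 0.0635 = 0.124

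That is 11 to 12 percentage points.

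**4. Shift in the estimate.** Imbalance x g runs from 0.114 x 0.2 = 0.023 SD to 0.124 x 0.5 = 0.062 SD.
- Against d = 0.2: 11% to 31%.
- Against d = 0.4 (if the target was really f = 0.2): 6% to 16%.
- Against the standard error, 2/sqrt(248) = 0.127 SD: at most 0.062/0.127 = 0.49.

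These are tail values. The median absolute shift is 0.674 x 0.0582 x 0.2 = 0.008 SD up to 0.674 x 0.0635 x 0.5 = 0.021 SD. With all 310 analysed, the 95% limits are 10 to 11 points and 0.020 to 0.056 SD.

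**5. Precision.** Share of variance explained = p(1-p)g²: 0.21 x 0.04 = 0.008 to 0.25 x 0.25 = 0.062. Ratio of standard errors = sqrt(1 - share): 0.9958 to 0.9682, a fall of 0.4% to 3.2%. Power of a two-sample test of change at d = 0.2 with 124 per arm rises from 35.0% to between 35.3% and 36.9%.

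**6. Validity.** In 20,000 simulated null trials (p = 0.5, g = 0.5, 124 per arm), type I error was 4.75% both without and with the covariate, and the mean estimate was 0.001 SD in both. The SD of the estimates was 0.126 without and 0.122 with adjustment.

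**7. How the term must enter.** With two visits, the group-by-time contrast is the arm difference in change. A covariate with a main effect only adds the same amount at both visits and cancels when one is subtracted from the other. Only a covariate-by-time term, or a covariate in a model for the week-8 value given baseline, acts on the contrast.

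**The case against.** The strongest case against has four parts.

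- **Silence is not exclusion.** The article gives no model formula and does not say the analysis is unadjusted; covariates may be set in a full protocol or analysis plan that is not shown. This stands. It can be said only that the model as described names no covariate. The point is still worth making, because the article does choose a response to medication, and for the primary estimate a better one is available.
- **Chance imbalance is already paid for.** A reader might infer that imbalance in antidepressant use biases or invalidates the primary comparison. The documents do not support that: allocation is randomised 1:1, and the unadjusted standard error already contains this variation, as step 6 shows.
- **Stable differences cancel.** The outcome is change. If users simply score higher or lower on the HDRS at both visits, nothing carries over; only an association with change matters, and the article gives no figure for it. This also stands, and it is why g is defined on change.
- **Why this covariate?** The same argument applies to number of previous episodes, age at onset or site. That is fair, and nothing in the article shows that antidepressant use is the better predictor. The reason to pick it is that the article itself flags it.

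The exclusion of participants after medication changes, set against an ITT primary analysis, is a separate matter that must be reconciled. It lends no weight to this point.

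**Conclusion.** The point holds as a minor improvement, not as an error. The article flags antidepressant use, records it, and names no place for it in the primary model. The primary comparison is nevertheless valid as described. Omission costs an estimated 0.4-3.2% in standard error and leaves in place a possible single-trial shift of 0.02-0.06 SD at the 95% limit of imbalance, typically much less. Both ranges rest wholly on the assumed share of users and the assumed difference in HDRS change; if antidepressant use is unrelated to change, there is nothing to gain. The trial's conclusion is unlikely to turn on this. The case for acting is that the change is almost free and settles the adjustment before the data are seen.

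**What to change.** Pre-specify baseline antidepressant use (yes/no), taken from the baseline record only, in the primary HDRS model, in one of two forms:

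- a covariate-by-time term in the repeated measures model; or
- a covariate in an ANCOVA of week-8 HDRS on baseline HDRS.

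A main effect alone in the repeated measures model would not do. The second form brings a larger gain of its own through baseline HDRS: at the article's correlation of 0.5 the residual SD falls to sqrt(0.75) = 0.866, and power at d = 0.2 with 124 per arm goes from 35.0% to 44.4% before medication is added.

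Do not adjust for medication started or changed after randomisation, since it may be a consequence of allocation. Because the history is taken again after the intervention, the text should name the baseline visit as the source. The sub-analysis can stay as a secondary analysis.

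Cost: one degree of freedom and a sentence in the analysis plan; no new data, visits or participants.

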For the purpose of this study and to facilitate the recruitment, the IFD tool is available in three languages: Spanish, Catalan and Basque, and patients are allowed to choose among versions according to their language preferences. Participants can access the PHQ-9 at any time, to assess their depression symptoms. A guide for interpreting the PHQ-9 scores is provided. If the patient responds positively to the item regarding suicide (i.e., “Thoughts that you would be better off dead or of hurting yourself in some way”) a message recommending seeking for emergency care will appear on the top of the screen. In addition, emergency contacts for Spain are listed on the website. The use of IDF tool is complementary to TAU which consists of monthly visits with the GP and pharmacological treatment with an ISRSS if needed.

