#### Active control group (internet-based psychoeducation + TAU)

Internet-based psychoeducation consists of a webpage containing information about MDD and healthy habits. This webpage (www.ifightdepression.com) was also designed by the EAAD consortium, and unlike the tool, workshops and tasks are lacking. The psychoeducative content of this website is restricted to information regarding healthy habits (healthy eating, physical activity, positive social contact and daily organization). In addition, information on the following topics is included: what is depression, signs and symptoms, diagnosing depression, subtypes of depression, brain function in depression, causes and an overview of depressions treatment (both pharmacological and psychological). Participants on this condition can also complete the online PHQ-9. This is an open-access webpage (i.e., a username and password are not required). Participants allocated to this condition will receive an e-mail with the page link and will be instructed to navigate freely throughout their content. As in the intervention group, TAU consists of monthly visits to the GP together with pharmacological treatment (if needed).

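### Excluding randomised participants for medication changes during the trial contradicts the ITT primary analysis and can bias it

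*Protocol article*

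**What the plan says.** The Statistical analysis plan section fixes the analysis set: "Primary analyses will be conducted on the Intention-To-Treat (ITT) sample". The endpoint there is the HDRS change from baseline to week 8. On incomplete data it says: "Missing data will be inspected and handled via full information maximum likelihood (FIML) or multiple imputations (MI) as appropriate".

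The Discussion gives a rule that acts after randomisation. Its stated reason is "Considering that the effects of the concomitant medication may impact our findings". The rule itself reads: "participants will be excluded from the study if drastic changes in their medication took place during the study period". Alongside this rule, the article plans a separate look at the drugs: "a sub-analysis evaluating the potential effects of antidepressant will be conducted". The article does not say what counts as drastic, who decides, or whether the week-8 HDRS of such a participant is still collected and analysed. The rule does not appear among the eligibility criteria under Study participants.

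Medication is also part of the background care being studied. In the intervention arm the tool complements "TAU which consists of monthly visits with the GP and pharmacological treatment with an ISRSS if needed". The section on the active control group defines TAU in the same way. The Discussion calls the design naturalistic and allows antidepressants alongside either intervention.

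**The concern.** An ITT analysis keeps everyone as randomised. A rule that removes people for something that happens after randomisation undoes this for exactly those people. The event is unlikely to be neutral: where drugs are given according to need, a marked change in medication tends to follow how the patient is doing, which is what the HDRS measures.

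Three things are at stake.

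- **The comparison.** Among the participants who remain, the arms are no longer balanced by randomisation if the tool affects symptoms and symptoms affect medication.
- **The question.** The objective is the effect of the tool added to TAU. TAU includes drug treatment as needed, so a result restricted to people without a marked medication change answers a different question.
- **The data.** If exclusion ends follow-up, the week-8 HDRS of these participants cannot be recovered at analysis.

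**Working it through.** **1. The passages side by side**

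| Place in the article | What it implies for a randomised participant whose medication changes markedly |
|---|---|
| Statistical analysis plan | Stays in the primary analysis (ITT) |
| Discussion | Is excluded from the study |
| Intervention and control descriptions | Drug treatment as needed is part of TAU in both arms |

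The first two rows conflict. The third shows that the trigger can lie within the care under study.

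**2. Size under a complete-case reading**

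The article's only relevant figure is the effect size d = 0.2 (Study participants). Everything else here is assumed:

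- the outcome Y has SD 1, and higher is worse;
- mid-trial state M has correlation ρ = 0.7 with Y;
- the tool lowers Y by δ and M by 0.7δ;
- anyone with M above a cut-off c is excluded, by the same rule in both arms;
- the medication change itself has no effect on Y.

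With c′ = c + 0.7δ, the retained mean is −ρφ(c)/Φ(c) in control and −δ − ρφ(c′)/Φ(c′) in the iFD arm. Hence

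estimated benefit = δ − ρφ(c)/Φ(c) + ρφ(c′)/Φ(c′).

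| δ | Excluded, control | c | c′ | ρφ(c)/Φ(c) | ρφ(c′)/Φ(c′) | Excluded, iFD | Estimate | Retained |
|---|---|---|---|---|---|---|---|---|
| 0.20 | 10% | 1.282 | 1.422 | 0.137 | 0.110 | 7.8% | 0.174 | 87% |
| 0.20 | 20% | 0.842 | 0.982 | 0.245 | 0.206 | 16.3% | 0.161 | 81% |
| 0.20 | 30% | 0.524 | 0.664 | 0.348 | 0.300 | 25.3% | 0.152 | 76% |
| 0.40 | 10% | 1.282 | 1.562 | 0.137 | 0.088 | 5.9% | 0.351 | 88% |
| 0.40 | 20% | 0.842 | 1.122 | 0.245 | 0.171 | 13.1% | 0.326 | 82% |
| 0.40 | 30% | 0.524 | 0.804 | 0.348 | 0.256 | 21.1% | 0.308 | 77% |

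A value of 0.40 is shown beside the protocol's 0.2 only to show that the proportion lost hardly depends on δ.

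A sharp cut-off is a strong form of selection. With a graded (logistic) dependence of exclusion on mid-trial state and about 5% to 28% excluded per arm, simulation gave 80% to 97% of the true effect retained. Across both mechanisms the loss is roughly 3% to 25%.

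**3. When there is no bias**

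- If δ = 0 and the rule is the same in both arms, c′ = c, the last two terms cancel and the estimate is 0.
- If exclusion is unrelated to symptoms, the simulated estimate stays at the true value within simulation error (0.20 and 0.40 with 10% excluded per arm).

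**4. Size if excluded participants are imputed**

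Take the sharp cut-off with δ = 0.40. Imputing week 8 from the mid-trial state that drives exclusion returns about 0.40 at all three exclusion rates, because missing-at-random then holds. With only a proxy correlated about 0.8 with that state, the results ran from about 0.34 to 0.39, depending on how the proxy was built. Imputation reduces the bias, and removes it only if the driver of exclusion is fully captured.

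**5. Numbers lost**

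Each 10% excluded is 0.10 × 310 = 31 randomised participants.

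**The case against.** The best defence is that exclusion means withdrawal: the participant stays in the ITT set and the missing week-8 HDRS goes to FIML or MI. PHQ-9 and RDQ are collected at weeks 2, 4 and 6 in both arms and could inform the imputation; step 4 shows that good auxiliary data can remove most of the bias. This stands as a limit on the size of the problem. It does not rescue the plan. The article neither gives that reading nor commits to auxiliary variables. The HDRS itself is taken only at baseline and at the post-intervention visit. The outcome would be lost on purpose, for a plausibly symptom-related reason, when it could simply be measured.

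It may also be said that one Discussion sentence condenses a fuller rule elsewhere. That is possible, but the sentence is worded as a plan, next to another planned analysis, and contradicts the stated analysis set.

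Some stronger readings are tempting and not supported:

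- **Unequal detection of changes between arms, hence false positives.** A reader might infer this because regular professional contact is described only for the iFD arm. However, that contact is for working through the material and technical support. Medical history, under which current drug treatment falls, is taken from everyone at baseline and at the post-intervention visit; the researcher doing those visits is blind to allocation; and both arms have monthly GP visits. No passage says who decides on exclusion.
- **Removal of the worst responders.** Drastic is undefined, and a change may also follow side effects or improvement.
- **Removal for receiving the comparator's care.** TAU is given in both arms, and no passage says that ordinary need-based prescribing counts as drastic.

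**Conclusion.** The contradiction is certain: the article declares an ITT primary analysis and also a post-randomisation exclusion. The bias is possible rather than certain. With a common symptom-driven rule, complete-case analysis and a working tool, about 3% to 25% of the true effect would be lost. For d = 0.2 that is an estimate of about 0.15 to 0.19. In that setting the bias is towards the null, so it would not by itself create a false claim of efficacy.

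These figures rest on the assumed correlation, triggers and exclusion rates, and on ignoring any effect of the medication change on the HDRS. Imputation with good auxiliary data would make them smaller. The article gives no rate of medication change, so confidence in the size is low. Confidence that the passages must be reconciled is high. This should be settled before any participant is excluded, because an uncollected week-8 HDRS cannot be restored.

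**What to change.** Reconcile the two sections as follows.

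1. Delete the post-randomisation exclusion from the Discussion.
2. State that every randomised participant is followed to the week-8 HDRS regardless of medication change, and that all are included in the primary ITT analysis.
3. Record the date and type of each medication change.
4. Confine any other handling to one labelled sensitivity analysis, for example setting HDRS after a marked change to missing and imputing it. Define beforehand which changes count for that analysis.
5. Optionally, base the planned antidepressant sub-analysis on use at baseline, which avoids conditioning on a post-randomisation event. The article does not say which use it means, so this is a suggestion and not a correction.

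The cost is a change of protocol wording, one extra analysis, and some concomitant-medication variability left in the outcome. The planned sample of 310 does not change. The fix concerns follow-up and analysis membership only; it proposes no rule on prescribing or on continuing either intervention.
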